| 2.4 | **Description and justification of the methods of use of the device and the duration of treatment:**  The playroom layout is designed to reduce the child's sensory perception: the light is diffused, the floor is soft, the sounds are damped, the games are stored on high shelves and the floor is is not cluttered with objects. A mirror on the wall, a swing are part of the basic equipment.  The volunteers follow each other in increments of one hour and a half (two in the morning, two or three in the afternoon). In phases 2 and 3, the child progressively left the playroom for external contacts, then for pre-school learning.  Additional care, is useful (speech therapy, psychomotricity or others) as they do not present learning modes contrary to the developmental approach 3I. Thus, assisted communication tools such as PECS are, in most cases, not recommended in the context of additional support. Likewise, learnings based on reinforcers other than mere verbal encouragement are not recommended.  The duration of 3I method usually lasts from two to three years. If the child starts from a relatively favorable level of development, it is possible (on average almost two out of ten according to the retrospective study of 120 children) that the child is admitted to class before the end of two years of care. |
| 2.5 | The research will be conducted according to the protocol with data record prior the beginning of the trial will be used for the purposes of the longitudinal study as soon as the parents have given explicit informed consent. |
| 2.6 | **Description of the population to study:**  An experimental group of 20 children with a diagnosis of Autism Spectrum Disorder who are not in school and benefiting from the 3I method between 30 and 35 hours per week will be recruited (Method 3I 'pure', without further intervention). The age of onset of care will range from approximately 2 to 12 years. Older children may be studied as well and may be the subject of separate studies. |

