| **5.1** | **Inclusion criteria**  **•** Child and adolescent diagnosed with ASD (criteria: ADI-R and CARS)  • Parental agreement and signed informed consent  • Child who starts the 3I method from January 2013  • Age between 2 years and 12 years at the beginning of the treatment 3I for the experimental group  • Consistent application of the method (adequate playroom, number of volunteers and number of hours of stimulation between 30-35h per week)  • Out-of-school child and adolescent who benefits from the 3I 'pure' method, without any other major intervention.  • Child with French in mother tongue |
| **5.2** | **Criteria of non-inclusion**  • Associated pathology (epilepsy, Rett syndrome ...)  • Child with Asperger syndrome  • Family situation that does not make it possible to consider taking care of 3I in the long term  • Children who do not do 100% of 3I method (part-time support)  • Child receiving other type ABA care, TEACCH |
| **5.3** | **Premature stop procedure:**  The regulation concerning the events and undesirable effects will be respected.  In the event of an undesirable effect (lasting aggravation of behavioral disorders)  In the case of significant improvement indicating partial or total re-enrollment  In case of unilateral decision of the family to leave the research and / or care 3I  In the first two cases, the investigator and the collaborating investigator, possibly solicited by a referent psychologist of the child, will decide on the premature exit of the study, having, as far as possible, carried out the tests so to limit the missing data (and also in the third case). |
| **6** | **Treatment other than the device:**  Additional interventions in speech therapy, psychomotricity, occupational therapy and other interventions that may require technical actions that are not the responsibility of 3I volunteers may be associated. These interventions will be recorded to analyze if they can biased the interpretation of the results. |
| **7** | **Performance evaluation:** |
| **7.1** | **Description of performance evaluation parameters:**  • The severity of autistic disorders (CARS)  • Homogeneity of development (PEP)  • The development of socio-communicative skills (IMITATION)  • Adaptive behavior (VABS) |

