| **9.4** | **Statistical criteria for stopping the search:**  If the interim analysis at T1 showed a significant deterioration of the measures of functioning of the children |
| **9.5** | **Method of taking into account missing data:**  • To take into account the missing data we will use alternative sources of information. For example, in the case where the child does not realize an item (for lack of interest) this information will be collected from the child's parents or psychologists. This information should be verified on written accounts of volunteers or video recordings of play sessions. If there is missing data in one of the tests, the subject data concerning the test in question will be excluded from the analysis.  • In the case of premature termination of the method (unilateral decision of the family) tests will be made to estimate the evolution of the child, even outside the scheduled timing for assessments. If it is impossible to carry out these tests, we will be able to use the last films of the working sessions to rate CARS and Vineland. In all cases, those lost to follow-up will have to be taken into account in the interpretation of the results because they could constitute a bias (children progressing insufficiently being more likely to stop care prematurely). |
| **9.6** | **Change management at the initial statistical level**  A priori not applicable |
| **10** | **Right of access to data and source documents**  The right of access to the data and source documents will be strictly reserved to the investigator, to the collaborator of the investigator and to the person in charge of the quality control (cf §11) |
| **11** | **Quality control and quality assurance**  The investigator's collaborator will work under the control of the investigator. The relatively repetitive nature of the tests performed did not seem to require the intervention of a third party in quality control and quality assurance. |

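### Section 9.5 excludes a child's test when data in it are missing; read naturally, this makes the mixed model a complete-case analysis although exits depend on progress

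*Protocol*

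**What the plan says.** Protocol Section 9.5 has two parts.

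- **Incomplete tests.** Items the child does not perform are first sought from parents or psychologists and checked against written accounts or videos. The paragraph then ends with the exclusion rule: "If there is missing data in one of the tests, the subject data concerning the test in question will be excluded from the analysis".
- **Early termination by family decision.** Here "tests will be made to estimate the evolution of the child, even outside the scheduled timing for assessments". If that is impossible, "we will be able to use the last films of the working sessions to rate CARS and Vineland". Losses to follow-up are to be weighed when results are interpreted, because of a possible bias: "children progressing insufficiently being more likely to stop care prematurely".

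Section 5.3 lists three reasons for leaving the study early: a lasting aggravation of behaviour, a decision of the family, and a third worded "In the case of significant improvement indicating partial or total re-enrollment". Tests are to be done at exit as far as possible in all three cases.

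Section 2.4 says that a child who starts from a fairly favourable level may be admitted to class before two years of care, "on average almost two out of ten according to the retrospective study of 120 children".

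Section 9.1 plans a mixed model with time at T0, T1 and T2, justified by power and the subject effect. Section 4.1 makes the Nadel imitation scale and the Vineland communication and socialization scores the main criteria. Section 9.2 gives about 20 children. Section 4.4 says that no control group could be formed.

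**The concern.** A mixed model can use a child's T0 and T1 scores when T2 is missing. The exclusion rule refers to the subject's data on the test, not to one visit, so its natural effect is to discard those scores too. The analysis then rests on children with complete data for that instrument.

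That would be mainly a loss of precision if children left for reasons unrelated to outcome. The protocol describes the opposite: poor progress, worsening and marked improvement can all lead to exit. The children who remain are then a selected group. With no control arm, the within-group change is the quantity that is tested and set against the literature, so any distortion in it passes straight into the conclusion. Weighing losses at the interpretation stage leaves the estimate as it is.

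**Working it through.** **No figure in the plan to reproduce.** Section 9.2 gives about 20 children without effect size, SD, power or loss rate. What follows is illustration on assumed inputs.

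**1. Precision.** Input from the protocol: n = 20 and α = 0.05. Assumed: two-sided test, 80% power, paired t-test. The detectable change d, in SDs of the paired change, solves P(|T′| > t(0.975, n-1)) = 0.80, where T′ is noncentral t with n-1 degrees of freedom and noncentrality d√n.

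| Children analysed | Detectable d | Power at d = 0.66 |
|---|---|---|
| 20 | 0.66 | 80% |
| 18 | 0.70 | 75% |
| 16 | 0.75 | 69% |
| 15 | 0.78 | 66% |
| 14 | 0.81 | 63% |

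**2. Bias when children without T2 are deleted.** Assumed: intercept SD 0.9, slope SD 0.35 per year, error SD 0.3, visits at 0, 1 and 2 years, true 24-month gain 0.50. Baseline SD is √(0.81 + 0.09) = 0.95, so the gain is about half an SD. Losses after T1 are drawn at random from the lower or upper half of T0-T1 progress.

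- SD of T0-T1 progress: √(0.35² + 2 × 0.3²) = √0.3025 = 0.55.
- Covariance of T0-T1 with T0-T2 change: 2 × 0.35² + 0.3² = 0.335.
- The mean of each half lies √(2/π) = 0.798 SD from the centre, so it shifts the T0-T2 change by 0.798 × 0.335/0.55 = 0.486.
- With L children lost from the lower half and H from the upper half, bias ≈ 0.486 × (L - H)/(20 - L - H).

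| L, H | Formula | Relative to 0.50 | Simulated complete-case estimate |
|---|---|---|---|
| 3, 0 (15%) | 0.486 × 3/17 = 0.086 | +17% | 0.58 |
| 5, 0 (25%) | 0.486 × 5/15 = 0.162 | +32% | 0.66 |
| 7, 0 (35%) | 0.486 × 7/13 = 0.262 | +52% | 0.75 |
| 0, 4 (20%) | -0.486 × 4/16 = -0.122 | -24% | 0.38 |
| 2, 2 | 0 | 0% | 0.50 |
| 2, 4 | -0.486 × 2/14 = -0.069 | -14% | 0.43 |

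The formula uses large-sample half-means, so it runs slightly above the simulation at n = 20. For lower-half losses a likelihood estimate on all observed visits stays at 0.50.

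**3. False positives.** With no true change, repeated simulations of the complete-case t-test reject in 6-7%, about 10% and 18-19% of trials at 15%, 25% and 35% loss from the lower half. With equal losses from both halves the rate is about 4%.

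**4. Sensitivity to the assumptions.**

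- A gain of 1.0 instead of 0.5 halves the relative bias: at 25% loss, 0.162/1.0 = 16%.
- If half of the exits yield a usable T2 score, the bias at 15%, 25% and 35% loss is about 8%, 14% and 20%, and false positives are 5.3%, 6.5% and 7.8%.
- A different data model (true change 0.80 SD, visit correlation 0.5 to 0.7, 10% to 30% missing T2) gives 0.84-0.93 under deletion when poor observed progress drives exit and 0.68-0.76 when good progress does. Likelihood on all visits gives 0.80 in both.
- If exit depends on the unseen T2 change, deletion gives 0.87-1.05 and likelihood 0.85-0.97: smaller bias, but not none.

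**The case against.** The case on the other side has four parts.

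- **Scope.** The sentence closes a paragraph about unperformed items. It could mean that one unscorable administration is dropped and the other visits stay, in which case the mixed model keeps its use of partial data. The text does not exclude this. It also does not say it, and the sentence names the subject's data rather than the visit's. The wording needs settling on either reading.
- **Salvage.** Deletion comes after an attempt to fill missing items, and early exits have their own provisions. A reader might infer that every early exit loses all its data; the documents do not support that, and for CARS and Vineland deletion should be rarer. But the films do not cover the Nadel scale or PEP-R. An off-schedule score also has no stated place in a model whose time levels are T0, T1 and T2.
- **Direction.** A reader might infer that the result is biased, and in favour of 3I. The protocol speaks only of a possible bias and describes exits in both directions, which may partly or wholly cancel.
- **Inputs.** Loss rates, SDs and gains are assumed. The almost two in ten of Section 2.4 concerns class admission in a retrospective series; it is not a rate of missing T2 data. Nor does the protocol choose the mixed model for its handling of incomplete data.

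These points limit the size and certainty of the concern. They do not defend the exclusion sentence. Section 4.4 attributes success to 3I only if it is massively superior to published data, which limits the claim but does not correct the estimate.

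**Conclusion.** The concern holds in a limited form. Section 9.5 states a rule that, read naturally, discards observed scores and makes the Section 9.1 model a complete-case analysis for the affected test. Because the protocol links exit to progress, the T0-T2 change **can** be biased; the net sign and size are unknown. Precision is also lost with about 20 children.

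The illustrated 16% to 50% overstatement requires one-sided exits of 15% to 35%, no salvage and a gain of 0.5 SD. The opposite pattern, with 20% lost, gives about -24%. The bias shrinks with salvage or a larger gain and is near zero if exits balance. The exposure is greatest for the Nadel imitation scale, where a main criterion has no fallback once exit testing fails, and for PEP-R.

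**What to change.** 1. In Section 9.5, replace the exclusion sentence with: *All available assessments of every included child enter the mixed model; only an unscorable administration is set to missing, and for that visit only.*
2. In Sections 9.1 and 9.5, state that off-schedule tests enter at their actual months of care, not as T1 or T2.
3. In Section 5.3, state that stopping 3I does not end the scheduled T1 and T2 assessments where the family agrees.
4. Name one sensitivity analysis for informative exit, for example no further gain after the last assessment. It may sit in the protocol or the analysis plan.

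Cost: mainly wording. Assessments at 12 and 24 months are already scheduled in Section 4.2, but Section 14 gives only a project total, so it cannot be said that visits for children who have stopped 3I are funded. Downside: the model relies on data missing at random and does not fully remove bias if exit depends on unseen scores, hence item 4.

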| **7.2** | **Methods and schedule for measuring, collecting and analyzing evaluation parameters:**  The quantitative methods used to measure performance changes will consist in comparing the results obtained at the different assessments at different periods of care (T + 1 month, T + 12 months, T + 24 months). The collection and analysis of intermediate data will be carried out progressively as the evaluations are carried out. The first analysis will be conducted at the end of the second evaluation period (T + 12 months), we will compare the data from all these tests, at T + 1months. period T + 12 months. A second analysis will be conducted at the end of the tests to compare the performance of the method between the three measurement periods (T + 1 month vs. T + 12 months vs. T + 24 months).  Through PEP-R (Schopler, 2005), we will conduct a performance analysis based on an assessment and direct observation of the child. The analysis will focus on two types of data collected: 1) the age of global and specific development corresponding to different areas of development (Imitation, Perception, fine motor skills, gross motricity, hand-hand coordination, cognitive performance, verbal cognition) and And 2) behavioral observations (relationships and affect, play and interest in the material, sensory responses, and language) collected during the assessment sessions. This tool, which gives a global and specific level of development for each evaluated domain, makes it possible to see the homogeneity of the development. The more the development becomes homogeneous during the 2 years of care, the better the performance of the 3I method.  Via the Scale of Imitation (Nadel, 2012), we will perform a detailed analysis of socio-communicative skills. This tool makes it possible to evaluate the level of the preverbal communication, in particular that of the imitation. It consists of three scales: spontaneous imitation, recognition to be imitated and imitation on request. The analysis of the scores obtained in these three sub-scales will make it possible to better follow the effect of this method on the development of nonverbal communication in very young or non-verbal subjects. An analysis of socio-emotional behavior (CPSE) based on a behavioral coding grid will measure the impact of the 3I method on the evolution of social-emotional behaviors (positive vs. negative). The higher the imitation scores and the number of positive social-emotional behaviors increase over the 2 years of care, the better the 3I method's performance.  These tests will be accompanied by 3 semi-structured interviews with parents (ADI-R, CARS, VABS). These are multidimensional assessments of learning and dysfunctions in everyday life.  The ADI-R which is a diagnostic assessment tool focuses on the description and history of child development in the three domains: quality of social interactions, communication and language, narrow interests and stereotyped behaviors. A change in scores on this parent questionnaire might reflect the impact of the method.  CARS, which is also a diagnostic tool, will allow us to assess the intensity of autistic disorders and their evolution during the trial. The 15 domains usually disturbed in autism are evaluated there: social relations, imitation, emotional response, use of the body, use of objects, adaptation to change, visual responses, auditory responses, taste-smell-touch (responses and modes of exploration), fear and anxiety, verbal communication, nonverbal communication, level of activity, intellectual level and homogeneity of intellectual functioning and general impression. The lower the overall score during trail, the better the performance of the 3I method.  The VABS which is a social adaptation assessment tool makes it possible to analyze, through the scores converted into developmental age (referred to mean equivalent ages of the normal sample), the impact of the 3I method on the development of socialization, communication, and the autonomy of everyday life. The more the difference between the chronological age of the subject and his age of development decreases during the management, the better the performance of method 3I. |

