| **8** | **Security assessment**  The 3I method is carried out in a family setting, with the exception of the center of Lud'éveil Courbevoie for five children. Child safety is ensured mainly by his parents. The equipment in the playroom provides a camera through which all sessions can be viewed.  The risk of exposure to pedophilia by volunteers is not to be neglected; it is lessened by the presence of another person in the immediate vicinity of the playroom, and by the recording of the camera, which any interruption would raise the mistrust of the parents.  The occurrence of any events or adverse effects, within the meaning of § 5.3 will be notified by the 3I psychologist assigned to the child to the investigator. |
| **9** | **Statistisques :** |
| **9.1** | **Description of planned statistical methods and timing of interim analyzes:**  Statistical methods: It will compare the mean of the scores or the ages of developments of the cohort obtained with the different tests of the evaluation carried out at T0, T1, T2. Once the conditions of application of the parametric tests are verified we will apply a general linear mixed model (GLMM) to obtain a better statistical power while taking into account the individual variations of the subjects (subject effect). Additional analyzes will take into account the age group of the child in covariate, as well as the severity of the disorders, and the level of language (evaluated at Vineland). Individual studies may be carried out.  Independent variable:  • Time: evaluation at T0, T1, T2  Dependent variables for each test:  • CARS: total score  • VABS: age of development by domain (4)  • PEP-R: overall development age, age of development by domain (7) IMITATION: score by domain (3), number of socio-emotional behavior (positive vs negative)  In addition, we will analyze the profiles of each subject to evaluate areas of evolution (case study).  Calendar of interim analyzes:  • Intermediate analysis on T1 tests compared to T0  • Final analysis on T2 tests compared to T0 |
| **9.2** | **Expected number of subjects to include and statistical justification:**  About 20 subjects in the experimental group 2 years-12 years to perform parametric tests. |
| **9.3** | **Degree of signification:**  The main effects and interactions will be considered significant if the p-value is lower than the risk α = 0.05 |

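### Off-schedule exit scores have no place in a group model whose time variable is only T0, T1 and T2, so they are either excluded or assigned to a visit at which they were not taken

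*Protocol*

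**What the plan says.** Four parts of the protocol bear on this.

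- **9.5 (missing data).** When the family ends the method early, "tests will be made to estimate the evolution of the child, even outside the scheduled timing for assessments". If testing is impossible, the last session films may be used to rate CARS and Vineland. The same section says that where a test has missing data, the subject's data for that test leave the analysis. It also expects children with insufficient progress to leave more often.
- **5.3 (premature stop).** For lasting worsening and for improvement leading to re-enrolment, the decision on exit is taken "having, as far as possible, carried out the tests so to limit the missing data (and also in the third case"). The third case is the family's own decision.
- **9.1 (statistical methods).** "we will apply a general linear mixed model (GLMM) to obtain a better statistical power while taking into account the individual variations of the subjects". The only independent variable is "Time: evaluation at T0, T1, T2", and the closing comparison is "Final analysis on T2 tests compared to T0". Outcomes include "VABS: age of development by domain (4") and the PEP-R developmental ages. Individual profiles are planned as case studies.
- **7.2 (schedule).** The end-of-study analysis is to "compare the performance of the method between the three measurement periods (T + 1 month vs. T + 12 months vs. T + 24 months").

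No section says at what time, or as which visit, an exit score enters the group model.

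**The concern.** The protocol makes an effort to obtain late information on children who leave, and gives limiting missing data as the reason. It then fixes a group analysis with three time points. A test at month 8 or month 18 belongs to none of them.

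The time label matters because VABS and PEP-R results are developmental ages, which normally rise with elapsed time. A score taken six months early but counted as T2 treats a shorter course as a full one. Section 4.4 states that no control group could be formed and that change will be judged against published data, so no concurrent arm cancels a timing error. The children affected are also those whose exit is likely to be related to progress. If the handling is chosen after the scores are seen, that choice can move the result.

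**Working it through.** The protocol gives no figure of its own on this point to reproduce. It states about 20 subjects (9.2) and visits at months 1, 12 and 24 (7.2), but no rate of progress, standard deviation or expected number of leavers. Those are assumed below.

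**1. The passages side by side.** Sections 9.5 and 5.3 collect scores at exit. Sections 9.1 and 7.2 analyse months 1, 12 and 24. A month-16 test lies 4 months from T1 and 8 months from T2; a month-8 test lies 4 months from T1. In the group model such a score is left out (and on one reading of 9.5 the child's other scores on that test go too), or it carries a label that is wrong by these gaps.

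**2. Error for one child when an exit score is labelled T2.** With a constant rate r (developmental months per calendar month) and exit at month m:

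- shortfall = r × (24 − m); full T0–T2 change = r × (24 − 1) = 23r
- relative shortfall = (24 − m)/23, whatever r is
- m = 18: 6/23 = 26%. At r = 0.4 this is 2.4 of 9.2 months; at r = 0.2 to 0.6 it is 1.2 to 3.6 months
- m = 16: 8/23 = 35%

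**3. Effect on the cohort mean.** With k such children of 20 who progress at the average rate, the relative shift is (k/20) × (24 − m)/23.

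- k = 4, m = 18: 0.20 × 26% = 5.2%, which is 0.48 months at r = 0.4 (0.24 to 0.72 for r = 0.2 to 0.6)
- m = 16: 3.5% for k = 2, 7.0% for k = 4, 10.4% for k = 6

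Section 2.4 reports that almost two in ten children entered class before two years. Applied to 20 children that is about 4, so k = 4 is not far-fetched. But those exits fall under 5.3 and not under the off-schedule sentence in 9.5, so k remains an assumption.

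**4. Direction and alternatives, by simulation.** Assumed: 20 children, mean slope 0.5 (SD 0.25), 4 leavers between months 13 and 22, linear courses, a random intercept and slope, known variance components. Estimated T0–T2 change in developmental months:

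| Handling of exit score | Fast progressers leave | Slow progressers leave |
|---|---|---|
| All children measured at month 24 | 11.45 | 11.49 |
| Labelled T2 | 10.38 (−1.07) | 11.27 (−0.22) |
| Labelled nearest visit | not shown | 11.64 (+0.15) |
| Dropped | 10.93 (−0.52) | 12.02 (+0.53) |
| Actual time, random slope | 11.28 (−0.17) | 11.67 (+0.18) |

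The largest error is 1.07/11.45 = 9%. Actual time is closer than dropping the score in both columns. It clearly beats the T2 label when fast progressers leave; when slow progressers leave, the labelling rules do about as well.

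**5. The random slope is needed.** With a random intercept only and slow leavers, actual time gave 12.35 against 11.54 with complete data. Dropping gave 13.02 and the T2 label 11.32.

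**6. Excluding the child altogether.** In a separate run (5 slow leavers, random-intercept visit model), excluding leavers gave 13.5 against 11.5 with complete data, an overstatement of 2.0/11.5 = 17%. That is selection bias and not a labelling error, but it is what the 9.5 exclusion sentence produces if read that way.

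**The case against.** The strongest reply is that visit windows and the mapping of unscheduled tests usually belong in a statistical analysis plan, which is not at hand. On that view, naming T0, T1 and T2 in 9.1 only lists the planned assessments. This has some force: the protocol states neither a carry-forward nor a nearest-visit rule. It does not remove the point, because the protocol itself commits to off-schedule scores, defines time without a place for them, and adds an exclusion rule that pulls the other way.

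A reader might infer more than the text supports in four ways.

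- **That every exit score must be mislabelled or wasted.** The case profiles in 9.1 can use such a score at its true date. The conflict is confined to the group analysis.
- **That a month-12 exit test counted as T2 shows the error at its worst (12/23 = 52% for the child).** A month-12 test is T1 and on schedule. Calling it T2 would be carrying a value forward, which the protocol does not propose.
- **That tests at any month are required for all leavers.** The off-schedule sentence in 9.5 covers only the family's own decision. Section 5.3 asks for tests as far as possible and does not mention timing.
- **That the plan always understates benefit.** The simulation shows errors both ways. Much of the bias from dropping scores comes from outcome-related exit, which 9.5 already acknowledges.

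**Conclusion.** The point stands for the group analysis and should be corrected. Sections 9.5 and 5.3 gather exit scores to limit missing data, while 9.1, 7.2 and the exclusion sentence in 9.5 leave them excluded or mistimed.

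The size is moderate and conditional. The 26% for a month-18 test labelled T2 needs only a constant rate. The shift of about 5% in the cohort mean also assumes 4 such children of 20 who progress at the average rate. Under the simulated values the choice of handling moves the result by up to about 9%, in either direction. No forced error of a known size or sign can be claimed.

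**What to change.** 1. Record the date of every test and of every film used for rating. Section 4.9 does not list test dates among the source data, so add them.
2. In 9.1, enter time as actual months from the first day of care, piecewise linear with a knot at month 12, with a random intercept and a random slope for each child. Report the modelled change from month 1 to month 12 and to month 24. The mean has three parameters, as many as the three visits, and reproduces the visit means when all tests are on schedule.
3. Amend the exclusion sentence in 9.5 so that a child's available scores, exit scores included, stay in the model.
4. Give a sensitivity analysis without the exit scores.

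The cost is a few sentences in 4.9, 9.1 and 9.5 and one more model run. There are three limits. Change is taken as linear within each year for off-schedule tests. The month-24 estimate for leavers extrapolates their course. Bias from outcome-related exit is reduced but not removed.
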